| **Design:** | OMEGCA will be a prospective non-interventional and translational cohort study enrolling patients undergoing routine peritoneal lavage cytology (PLC) and subsequent curative-intent treatment (either upfront surgery or perioperative systemic treatment and surgery) for gastroesophageal cancer at hospitals across Victoria and South Australia.  Tumour biopsies, blood and peritoneal lavage fluid will be collected during routine pre-treatment PLC for all patients. A subset of patients will have a blood and peritoneal lavage fluid collected at the time of surgical resection, and blood collected at the first post-surgical follow-up clinic.  These samples will be centralised to a research laboratory at the Peter MacCallum Cancer Centre for processing and analysis. Part of the collected biospecimens will undergo methylomic analysis at the Peter MacCallum Cancer Centre, VIC. The remaining biospecimens will undergo genomic whole exome sequencing analysis at the Johns Hopkins University Hospital, and Haystack Oncology, USA. Methylomic and genomic analyses are aimed at detecting the presence of tumour derived DNA in peritoneal fluid (ptDNA). ptDNA status will be correlated to different clinical outcomes including patient survival.  Recruitment and sample analysis will be conducted over 2 years with clinical follow-up extended to 5 years from the last patient to capture disease free and overall survival data.  The final analytical cohort will include at least 200 patient samples. Part of this cohort will include around 100 patient samples and clinical data already collected as part of a pre-existing Peter Mac led translational project entitled ‘*Improving outcomes in gastroesophageal cancer*’ (HREC/44873/PMCC-2018, Project No: 18/211), which has a compatible study design to this project. |
| **Lead Study Centres:** | Peter MacCallum Cancer Centre |
| **Participating Hospitals:** | 10 to 12 sites |
| **Primary Objectives:** | 1. To determine whether pre-treatment ptDNA, detected using genomic and methylomic approaches, predicts disease free survival (DFS) in gastroesophageal cancer patients |
| **Secondary Objectives** | 1. To analyse the ability of methylomic and genomic assays, in comparison and in combination, to detect ptDNA and predict DFS and overall survival (OS). 2. To compare the performance of ptDNA vs. conventional staging methods (PLC, PET/CT) to predict histopathological features of the tumour, patterns of disease recurrence, DFS and OS. |

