# **Study Design**

### Study Type, Design, Schedule & Methodology

STUDY TYPE:

- Prospective non-interventional cohort study
- This study will include a cohort of patients who have undergone identical biospecimen collection, clinical treatments, and follow-up from Project No: 18/211, entitled ‘*Improving outcomes in gastroesophageal cancer*’ (HREC/44873/PMCC-2018)

ABOUT PROJECT NO: 18/211:

- Relevant to this study, project No: 18/211, entitled ‘*Improving outcomes in gastroesophageal cancer*’ (HREC/44873/PMCC-2018) was in part (as it was multi-facetted with different aims), a multi-centre biospecimen (tumour and normal tissue, blood, and peritoneal fluid) and clinical data collection project.
- Project 18/211 established the collaborative research network and generated the critical pilot data (11 patients) for this proposed study. The patient cohort recruited through Project 18/211 are identical to this proposed study.
- To avoid wastage of patient samples, research cost, human resources, and time, we propose that eligible patients who have undergone identical biospecimen collection, clinical treatments, cancer surveillance and follow-up in Project 18/211 as this proposed study, to be combined for the purpose of data analysis.

STUDY PERIOD:

- Participant recruitment: 2 years
- Clinical follow-up: Follow-up for 5 years after the last enrolled patient

STUDY SAMPLE SIZE:

- Merging of participants from this study and Project No: 18/211
- Combine total participant ≥200 based on power calculation, please see below and in section 8.

STUDY POPULATION:

- All patients with gastroesophageal junction and gastric cancer
- ≥ 18 years-of-age
- Without distant organ, non-regional nodal or gross peritoneal metastases
- Undergoing staging laparoscopy with peritoneal lavage cytology (PLC)
- Undergoing curative-intent treatment (either upfront surgery or chemo/radiotherapy and surgery) for their cancer

DESIGN SUMMARY TO ACHIEVE OBJECTIVES:

- This prospective, multicentre observational cohort study will enrol patients undergoing PLC and subsequent curative-intent treatment for gastroesophageal cancer.
- Tumour and normal (stomach and oesophagus) tissue biopsies, blood, and peritoneal lavage fluid will be collected during pre-treatment staging for all patients.
- A subset of patients (those who undergo neoadjuvant chemo/radiotherapy) will have tumour tissue, blood and peritoneal lavage fluid collected at surgery.

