**Addition to standard-of-care procedures**

| **Clinical Schedules** | **Timing (location) of assessments/procedures**  **Assessment/Procedure** | **Staging Laparoscopy**  **(Theatre)** | **Surgical Resection**  **(Theatre)** | **Post-operative**  **follow-up**  **(Clinic)** |
| --- | --- | --- | --- | --- |
|  | **Research blood collection** | **X** | **X** | **X** |
|  | **Research normal and tumour tissue biopsies** | **X** |  |  |
|  | **Research peritoneal lavage collection** | **X** | **X*** |  |

* Only applicable to participants who undergo neoadjuvant therapy.

- *Research blood collection*: 20-30 ml of peripheral blood will be collected prior to skin incision or in outpatient setting.
- *Research normal tissues biopsies*: 4-6 endoscopic biopsies of normal gastric and oesophageal mucosa
- *Research primary tumour biopsies*: 8-12 endoscopic biopsies of primary tumour
- *Peritoneal lavage fluid collection*: 150-250 ml of 500 ml 0.9% saline following 4 quadrant lavage of the abdominal cavity

STANDARDISING PERITONEAL LAVAGE COLLECTION AT STAGING LAPAROSCOPY:

During staging laparoscopy, there is currently NO standardised practice of performing peritoneal lavage. Between centres, there is variability with respect to the volume of saline (typically range from 0 ml to 1 L) applied and the quadrants of the abdomen (typically range from upper 2 quadrants to 4 quadrants) that are washed. Additionally, the pathology department within each hospital typically process and analyse variable amounts of submitted peritoneal lavage fluid. The remainder of this fluid is discarded. Therefore, in this study, we will standardise peritoneal lavage at staging laparoscopy to 500 ml 0.9% saline wash of all 4 quadrants of the abdomen. From this 300 ml will be submitted to anatomical pathology for routine processing and cytological analysis, and 200 ml will be used for ptDNA detection and analysis.

STANDARDISING PERITONEAL LAVAGE COLLECTION AT SURGICAL RESECTION:

For patients who have undergone neoadjuvant therapy, a further peritoneal lavage will be performed at surgical resection. Peritoneal lavage will be performed as soon as possible after achieving peritoneal access (either laparoscopically or via laparotomy). This will involve 500 ml 0.9% saline wash of all 4 quadrants of the abdomen. From this 200 ml will be used for ptDNA detection and analysis. The remaining 300 ml will be discarded.

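### About half the cohort is pooled from Project 18/211 as having identical specimen collection, but the protocol never shows that its peritoneal lavage was the same, and it sets no way to check

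*Protocol*

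**What the plan says.** The synopsis (Design) says: "The final analytical cohort will include at least 200 patient samples". It adds: "Part of this cohort will include around 100 patient samples and clinical data already collected". These come from Project 18/211, "which has a compatible study design to this project".

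Section 5a (About Project No: 18/211) uses stronger words. It proposes to combine "eligible patients who have undergone identical biospecimen collection, clinical treatments, cancer surveillance and follow-up in Project 18/211" with the new patients, and it also states: "The patient cohort recruited through Project 18/211 are identical to this proposed study".

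Section 5b (Standardising peritoneal lavage collection at staging laparoscopy) says: "During staging laparoscopy, there is currently NO standardised practice of performing peritoneal lavage". It describes variation between centres in saline volume (0 ml to 1 L), in quadrants washed (upper two to all four) and in the amount of fluid that pathology departments process. As a consequence, "in this study, we will standardise peritoneal lavage at staging laparoscopy to 500 ml 0.9% saline wash of all 4 quadrants of the abdomen", with 300 ml going to cytology and 200 ml to ptDNA.

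Section 8a defines groups 1 to 4 by cytology status and ptDNA status and powers the study on group 1 v group 2.

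**The concern.** Lavage fluid is the specimen for both variables that define the groups. If volume, coverage or aliquot differed between the two sources, the chance of a positive cytology or ptDNA result could differ too, and group membership would then depend partly on where and when a patient was recruited. The 18/211 patients were enrolled earlier, so source also carries calendar period, mix of centres and possibly treatment and length of follow-up. If positivity and DFS both vary with source, an unstratified comparison of groups 1 and 2 mixes the ptDNA effect with a source effect.

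The pooling condition in section 5a is meant to prevent this. The protocol does not say which items must match, which record shows it, who decides, or whether the decision precedes the ptDNA result.

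**Working it through.** **1. The passages side by side**

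| Question | Where | Answer |
|---|---|---|
| How large is the 18/211 share? | Synopsis | about 100/200 = 50% |
| On what terms is it pooled? | Section 5a | identical collection, treatment, surveillance and follow-up |
| How is its design described? | Synopsis | compatible |
| Is lavage uniform at present? | Section 5b | no: 0 ml to 1 L, two to four quadrants, variable volume processed |
| When is it made uniform? | Section 5b | in this study, future tense |
| What lavage did 18/211 use? | nowhere in the readable text | not stated |
| How is sameness verified? | nowhere in the readable text | not stated |

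Sameness is therefore asserted in one place, softened in another, and put in doubt by a third. None of the three gives the fact that would settle it.

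**2. The plan's own figure.** Section 8a gives 175 v 25 patients, 2-year DFS of 70% v 40%, 80% power and alpha 0.05; the test and its sidedness are not stated. A two-sided Fisher exact test, by full enumeration, gives 80.9%. A two-sided pooled z-test gives 83.6%. The stated size reproduces, and nothing here disputes it.

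**3. Would a poorer wash in 18/211 cost power relative to plan?** Assume, for illustration only, that 18/211 lavage detects 60% of the ptDNA-positives that the standardised wash would. Take 100 patients per source, all cytology-negative, with true positives at 40% DFS and true negatives at 70%. The answer depends on which source the planned 12.5% (1 in 8) describes.

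- *If 12.5% is the yield of the new wash:* missed positives = 100 × 0.125 × 0.40 = 5. Group 2 = 25 − 5 = 20 and group 1 = 180. Group 1 DFS = (175 × 0.70 + 5 × 0.40)/180 = 69.2%. Fisher power = 71.1%.
- *If 12.5% is the 18/211 yield:* the new wash yields 0.125/0.60 = 20.8%. Group 2 = 12.5 + 20.8 = 33.3, about 33. Missed positives in 18/211 = 20.8 − 12.5 = 8.3. Group 1 is about 167, with DFS = (158.3 × 0.70 + 8.3 × 0.40)/166.7 = 68.5%. Fisher power = 85.5%. At 80% relative yield the same steps give 28 v 172 and 82.3%.

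Section 8a takes 1 in 8 from the pilot data, and section 5a says that Project 18/211 generated those data (11 patients). Three of the 11 were cytology-positive, which leaves 8, of whom one was ptDNA-positive. So the second reading fits the documents better, and under it power rises.

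**4. What if 18/211 patients were dropped?** If none qualified and about 100 patients remained, split about 88 v 12 and all assumed cytology-negative, Fisher power would be 47.2%. This is an outer bound, not a forecast. It shows why removing patients freely is not a safe remedy.

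**The case against.** The strongest reply is that no difference has been shown. Section 5b describes routine practice between centres, whereas Project 18/211 was a dedicated multicentre biospecimen collection that may have had its own fixed lavage. Figures 4 and 5 and the laboratory manual, which might record it, are not visible. This stands. A reader might infer from section 5b that the 18/211 samples were taken with unstandardised lavage; the text does not say so.

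Second, section 5a already restricts pooling to patients with identical collection, so it would be wrong to say that no restriction exists. This also stands. What is missing is a way to apply the restriction reproducibly.

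Third, a reader might infer that poorer lavage in 18/211 shrinks group 2 and takes power to about 71%. That figure treats 12.5% as the yield of the new wash, but it comes from 18/211 pilot patients. The direction of any effect on power relative to plan is not established. Section 8a also reviews the ptDNA-positive share at 1 and 2 years and adjusts recruitment if it is below 10%.

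Fourth, stratification and sensitivity analyses are commonly left to the SAP, and section 8b already foresees covariate adjustment. That is fair, so their absence is not itself the finding. The pooling condition, however, is set in the protocol, and it is the protocol's own sections that do not agree.

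**Conclusion.** The point holds as a gap in documentation and an avoidable risk of confounding. For about half the cohort the protocol asserts, but does not show, that the specimen behind both grouping variables is the same as in new recruits. Its synopsis, section 5a and section 5b do not fit together on this.

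The size of any bias cannot be computed from the documents: it needs the 18/211 lavage procedure and the relation of source to both positivity and DFS. If lavage was the same in both sources, the specimen part of the concern disappears, though centre and period would still differ by source. The documents support neither a proven difference in lavage nor a stated loss of power.

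**What to change.** 1. Reconcile the synopsis, section 5a and section 5b: state the lavage volume, quadrants and aliquots used in Project 18/211, and use one description of its relation to this study.
2. Say which items must match for collection to count as identical and which operative or laboratory records show it. Complete the check before ptDNA results are seen.
3. Stratify the group 1 v 2 Cox comparison by source (18/211 v OMEGCA), in the protocol or the SAP.
4. Report ptDNA and cytology positivity by source.
5. Add a sensitivity analysis limited to patients with documented 500 ml four-quadrant lavage, the standard that section 5b sets for this study.

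Do not remove 18/211 patients from the primary comparison only because no record exists: nothing shows that the records hold these details, and the loss could be large (step 4 of the working).

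The cost is a records check on about 100 patients and one stratification factor already known for everyone. If the 18/211 lavage was in fact the same, the specimen question closes with one sentence.

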### Standard Care and Additional to Standard Care Procedures

OMEGCA is a prospective cohort study. Standard-of-care (i.e., disease staging, treatment, and follow-up) will not be affected or altered by research encounters and collection of specimens. Biospecimen collections which are additional to standard-of-care include blood collections at all clinical timepoints, biopsy of tumour and peritoneal lavage fluid collection at surgical resection.

**Standard-of-care procedures**

| **Clinical Schedules** | **Timing (location) of assessments/procedures**  **Assessment/Procedure** | **Pre-surgical visits**  **(Clinic)** | **Staging Laparoscopy**  **(Theatre)** | **Surgical Resection**  **(Theatre)** | **Post-operative**  **follow-up**  **(Clinic)** | **Long-term follow-up**  **1-5 years**  **(Clinic)#** |
| --- | --- | --- | --- | --- | --- | --- |
|  | **Demographic history** | **X** |  |  |  |  |
|  | **Clinical history** | **X** | **X** | **X** | **X** | **X** |
|  | **Histopathology** |  |  |  | **X** |  |
|  | **CT and PET** |  |  |  | **X** | **X** |
|  | **Endoscopy follow-up** |  |  |  | **X** | **X** |
|  | **Venepuncture, Blood collection** |  | **X** | **X** | **X** |  |
|  | **Endoscopy and tissue biopsies** |  | **X** |  |  |  |
|  | **Peritoneal lavage** |  | **X** |  |  |  |
|  | **Survival and recurrence follow-up** |  |  |  |  | **X** |

**Addition to standard-of-care procedures**

| **Clinical Schedules** | **Timing (location) of assessments/procedures**  **Assessment/Procedure** | **Staging Laparoscopy**  **(Theatre)** | **Surgical Resection**  **(Theatre)** | **Post-operative**  **follow-up**  **(Clinic)** |
| --- | --- | --- | --- | --- |
|  | **Research blood collection** | **X** | **X** | **X** |
|  | **Research normal and tumour tissue biopsies** | **X** |  |  |
|  | **Research peritoneal lavage collection** | **X** | **X*** |  |

* Only applicable to participants who undergo neoadjuvant therapy.

- *Research blood collection*: 20-30 ml of peripheral blood will be collected prior to skin incision or in outpatient setting.
- *Research normal tissues biopsies*: 4-6 endoscopic biopsies of normal gastric and oesophageal mucosa
- *Research primary tumour biopsies*: 8-12 endoscopic biopsies of primary tumour
- *Peritoneal lavage fluid collection*: 150-250 ml of 500 ml 0.9% saline following 4 quadrant lavage of the abdominal cavity

STANDARDISING PERITONEAL LAVAGE COLLECTION AT STAGING LAPAROSCOPY:

During staging laparoscopy, there is currently NO standardised practice of performing peritoneal lavage. Between centres, there is variability with respect to the volume of saline (typically range from 0 ml to 1 L) applied and the quadrants of the abdomen (typically range from upper 2 quadrants to 4 quadrants) that are washed. Additionally, the pathology department within each hospital typically process and analyse variable amounts of submitted peritoneal lavage fluid. The remainder of this fluid is discarded. Therefore, in this study, we will standardise peritoneal lavage at staging laparoscopy to 500 ml 0.9% saline wash of all 4 quadrants of the abdomen. From this 300 ml will be submitted to anatomical pathology for routine processing and cytological analysis, and 200 ml will be used for ptDNA detection and analysis.

STANDARDISING PERITONEAL LAVAGE COLLECTION AT SURGICAL RESECTION:

For patients who have undergone neoadjuvant therapy, a further peritoneal lavage will be performed at surgical resection. Peritoneal lavage will be performed as soon as possible after achieving peritoneal access (either laparoscopically or via laparotomy). This will involve 500 ml 0.9% saline wash of all 4 quadrants of the abdomen. From this 200 ml will be used for ptDNA detection and analysis. The remaining 300 ml will be discarded.

## **Study Population**

### Recruitment Procedure

All patients referred to the listed health networks with gastroesophageal cancer for curative-intent treatment will be considered for recruitment. All patients who fulfill study eligibility criteria (section 6b) will be able to participate in this study. Potential study participants will be identified through hospital outpatient clinics, approached by the treating clinician, local PI, and/or research fellow, and a verbal description of the study together with the patient information consent form will be provided. Professional interpreters may be used where appropriate to translate the discussion. Identification and recruitment of patients, as well as data collection will be performed by health professionals that are part of the clinical team who provide care for patients.

### Inclusion Criteria

- All patients ≥18 years-of-age at time of signing consent
- Have a histologically confirmed diagnosis of one of the following:
  - Gastric adenocarcinoma
  - Gastroesophageal junction adenocarcinoma
- Is undergoing staging laparoscopy and peritoneal lavage cytology
- Provides informed consent

### Exclusion Criteria

- Strictly oesophageal cancer
- Distant organ disease on CT and PET/CT
- Non-regional nodal disease on CT and PET/CT
- Peritoneal carcinomatosis on CT and PET/CT
- Undergoing emergency surgery
- Performance status ECOG ≥3 (Appendix 1.1)
- Palliative-intent treatment

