## **Introduction/Background Information**

### Lay Summary

The staging of stomach and oesophageal cancer is crucial for determining whether this disease is curable or not. This information allows patients and doctors to select the right treatment approach. Stomach and oesophageal cancers have a high likelihood of spreading to the abdominal cavity (peritoneum). The presence of peritoneal disease is currently considered incurable. Unfortunately, despite our best staging tests (CT and PET scans, and peritoneal washings to detect cancer cells), our ability to accurately stage the peritoneum is inadequate. This means that many patients are being offered aggressive and morbid treatments with potentially little benefit. Therefore, an accurate test to stage the peritoneum is urgently needed to personalise treatment and avoid over-treating patients with stomach and oesophageal cancer. ptDNA is cancer-derived DNA detectable in peritoneal washings. As this is a molecular test, we propose that ptDNA detection should be more accurate than current methods to stage the peritoneum. In our laboratory, we have developed the assays to detect ptDNA.

In the OMEGCA study (Multi-Omics Evaluation of Peritoneal Fluid in Gastroesophageal Cancer), we will recruit at least 200 patients with stomach and oesophageal cancer, and test their peritoneal washings, collected as part of routine staging, for ptDNA. We will compare the performance of two different methods to detect ptDNA, and determine whether ptDNA positivity correlates with patient survival, tumour characteristics and patterns of cancer recurrence.

If successful, this study will produce a novel and accurate molecular test to detect microscopic peritoneal cancer deposits. This information will improve disease prognostication, facilitate patient counselling, inform clinical decision-making, and personalise cancer treatment to maximise benefit and reduce harm.

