### Background information

ACCURATE STAGING IS CRITICAL FOR TREATING GASTROESOPHAGEAL CANCER

The incidence of gastroesophageal cancer has risen markedly and now ranks as the 4^th^ most common cause of cancer-related deaths in the world.^3^ It is a lethal diagnosis with a 5-year survival of 20-35%, and of greatest concern is the rising incidence in young adults (aged <50 years).^1, 2^ Accurate staging of gastroesophageal cancer is crucial for determining prognosis, treatment intent and approach. Staging typically involves endoscopy, PET/CT imaging and peritoneal lavage cytology (PLC). PLC involves irrigating the peritoneal cavity with saline and retrieving this fluid to assess for the presence of cancer cells. Patients without demonstrable distant organ or peritoneal disease (~40%) are treated with chemotherapy and radical surgery in the belief that aggressive and *potentially morbid* treatment will deliver a cure. However, the vast majority of these patients have locally advanced disease which carries a high risk for trans-coelomic spread into the peritoneum. Unfortunately, the presence of peritoneal metastases is currently considered incurable.^4^ Therefore, early and accurate detection of peritoneal disease, especially micro-metastases, is critical as it alters treatment intent and approach, either through avoiding morbid and futile treatments or enrolling into clinical trials such as studies evaluating peritoneal-directed therapy.

CLINICAL URGENCY: OUR ABILITY TO ACCURATELY STAGE THE PERITONEUM IS POOR

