### Study Objectives

PRIMARY OBJECTIVE:

1. To determine whether pre-treatment ptDNA, detected using genomic and methylomic approaches, predicts DFS in gastroesophageal cancer patients.

SECONDARY OBJECTIVES:

1. To analyse the ability of methylomic and genomic assays, in comparison and in combination, to detect ptDNA and predict DFS and OS.
2. To compare the performance of ptDNA vs. conventional staging methods (PLC, PET/CT) to predict histopathological features of the tumour, patterns of disease recurrence, DFS and OS.

EXPLORATORY OBJECTIVES:

1. To compare the cost-effectiveness of genomic vs. methylomic approaches to detect ptDNA to inform translation into clinical practice.
2. To compare ptDNA detection rates before (at time of PLC) and after (at time of surgical resection) neoadjuvant therapy.
3. To curate and catalogue actionable molecular targets identified from whole exome sequencing of peritoneal wash fluid to inform future clinical trials.
4. To compare ptDNA versus circulating tumour DNA (i.e. plasma) to predict sites and patterns of disease recurrence.

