### Consent

Patients who agree to participate in the project will be consented by a member of the treating team, local PI or local sub-PI affiliated with this project. The participant’s competence and capacity to consent to the study will be assessed by one of these members. Any patient who is not able to give valid, informed consent for themselves will not be considered for inclusion. Patients will be asked to consent to the collection of biospecimens and associated data as detailed in section 5a. They will also be asked to consent to the storage and future use of these samples and data. All procedures will be conducted in accordance with the Declaration of Helsinki. Please refer to the Patient Information and Consent form for more details.

The consent process will occur significantly ahead of any clinical procedure. The clinician/investigator will allow time to answer any questions from the patient regarding the project and provide the patient time to consider their involvement. The clinician will also emphasize that the standard of care will not be altered in any way, regardless of the patient’s consent. On the morning of staging laparoscopy/endoscopy and definitive surgery, the project will be discussed again with participants. They will be given the opportunity to ask questions. For participants who have already given consent, local investigators will verbally re-affirm their consent prior to the start of their procedure and the collection of samples. For potential participants who have not yet signed the consent form, they will be asked if they wish to sign the form before their procedure. Patients are under no obligations to sign the consent form, and for those who have signed and then changed their mind, they may withdraw consent at any time (See below 7b, Handling of withdrawals for further detail).

The clinician/investigator will facilitate signing of the PICF and provide the participant with a copy. A copy of the PICF will be added to the participants medical records. The original PICF will be digitised and stored locally in keeping with each institution’s practices. The hardcopy will be kept in a locked filing cabinet in a locked office.

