# **Statistical Methods**

### Sample Size Estimation & Justification & Power Calculation

POWER JUSTIFICATION:

OMEGCA will have 4 observational cohorts as listed below:

- Group 1: Peritoneal lavage cytology-negative & ptDNA-negative
- Group 2: Peritoneal lavage cytology-negative & ptDNA-positive
- Group 3: Peritoneal lavage cytology-positive & ptDNA-negative
- Group 4: Peritoneal lavage cytology-positive & ptDNA-positive

However, as the primary objective of this study is to evaluate the clinical utility of ptDNA as a biomarker to predict the primary endpoint (2-year DFS) in gastroesophageal cancer patients with no apparent micro-metastatic disease in the peritoneum (using current ‘best practice’ staging methods), we have powered this study to compare groups 1 and 2, as these are the patients with *peritoneal lavage cytology-negative* disease. Accordingly, we deemed a 30% absolute DFS difference at 2 years post staging laparoscopy as clinically significant between groups 1 and 2. This is based on our hypothesis that patients who are ptDNA-positive should by definition have cytology-positive disease, even if this was not detected. The conservative estimate of 2-year DFS in patients who are cytology-positive versus cytology-negative is 40% versus 70%, respectively. Using our pilot data (Figure 3), we anticipate approximately 1 in 8 patients who is cytology-negative will be ptDNA-positive, this means an enrolment ratio of 7 to 1 in groups 1 and 2, respectively. To detect a 30% absolute difference in 2-year DFS between these two groups, we would need to enrol 200 patients with 175 patients in group 1 (ptDNA-negative arm) and 25 patients in group 2 (ptDNA-positive arm) to reach 80% statistical power at an alpha <0.05.

INTERIM ANALYSIS:

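### The undated palliative-intent exclusion and resection-based DFS and OS let a cytology result remove its own positives, which tilts the sensitivity comparison of ptDNA with cytology towards ptDNA

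*Protocol*

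**What the plan says.** The Exclusion Criteria (section 6c) list "Palliative-intent treatment" with no time point, and the Synopsis has an equivalent line. Peritoneal disease excludes a patient only when it is seen on imaging; positive cytology is not a listed exclusion.

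The order of events is as follows.

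- Consent (section 6d): "The consent process will occur significantly ahead of any clinical procedure", and at the latest on the day, before the procedure starts. The same wash supplies fluid for cytology and for ptDNA (section 5b).
- Treatment follows cytology. The Synopsis describes "enrolling patients undergoing routine peritoneal lavage cytology (PLC) and subsequent curative-intent treatment".
- Staging, which the Background says includes lavage cytology, directs treatment: "Patients without demonstrable distant organ or peritoneal disease (~40%) are treated with chemotherapy and radical surgery". The same section says that "the presence of peritoneal metastases is currently considered incurable".
- ptDNA results are not returned to participants, apart from rare incidental findings (section 11a), and research procedures do not alter care (section 5b).

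Study Endpoints (section 4c) start both DFS and OS at surgical resection, and the surveillance timetable in section 5a is indexed by time since surgery. Section 8a, by contrast, places its 2-year DFS difference at 2 years after staging laparoscopy.

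Secondary objective 2 is "To compare the performance of ptDNA vs. conventional staging methods (PLC, PET/CT) to predict histopathological features of the tumour", and also recurrence patterns, DFS and OS. Section 8a plans two cytology-positive cohorts, group 3 (ptDNA-negative) and group 4: "Group 4: Peritoneal lavage cytology-positive & ptDNA-positive".

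**The concern.** One of the two tests being compared can change who is analysed, and the other cannot. If a positive cytology result changes the aim of treatment, the patient can meet an exclusion criterion after having been sampled. Even if the patient is not formally excluded, without a resection there is no DFS or OS under the definitions and no follow-up timetable. The cytology-positive patients who remain are those still judged suitable for curative treatment.

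What is at stake is the claim that ptDNA is more sensitive than cytology, which the Background puts forward as a main reason for the assay. Part of an observed advantage could come from the loss of cytology-positive patients and not from the assay. An analysis plan cannot repair this later, because eligibility, time origin and follow-up are set in the protocol.

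**Working it through.** **The plan's own figure.** Section 8a asks for 175 + 25 = 200 patients in groups 1 and 2, with 2-year DFS of 70% v 40%, 80% power and alpha 0.05 (two-sided assumed). Fisher's exact test, enumerated over all outcomes with event risks 0.30 and 0.60, gives 80.9% power, so the figure reproduces. Both groups are cytology-negative, so losing cytology-positive patients does not enter it.

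**Inputs for the comparison of tests.**
- Pilot mix (Background): of 11 patients, 3 were cytology-positive, all of them ptDNA-positive, and 1 was cytology-negative and ptDNA-positive. That leaves 11 - 3 - 1 = 7 negative on both. Groups 1 to 4 are 7, 1, 0 and 3.
- Two-year event risk (section 8a): 1 - 0.70 = 0.30 in group 1, and 1 - 0.40 = 0.60 where either test is positive.
- Assumed: a share f of groups 3 and 4 is lost, equal in both groups (ptDNA is not reported back) and unrelated to outcome. The protocol gives no value, so f runs from 0 to 1.

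**Formulas.** E1 to E4 are the expected events with nobody lost, k = 1 - f, and T = E1 + E2 + k(E3 + E4).
- Cytology sensitivity = k(E3 + E4)/T
- ptDNA sensitivity = (E2 + kE4)/T
- Difference, ptDNA minus cytology = (E2 - kE3)/T, that is, (group 2 events - group 3 events)/all events

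The derivative of the difference with respect to k is -[E3(E1 + E2) + E2(E3 + E4)]/T², which is never positive. Losing cytology-positive patients therefore moves the difference towards ptDNA. The exception is when groups 2 and 3 have no events, where the difference is zero while any positives remain.

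**Pilot mix.** E1 = 7 × 0.30 = 2.1, E2 = 1 × 0.60 = 0.6, E3 = 0, E4 = 3 × 0.60 = 1.8.

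| Share lost | T | Cytology | ptDNA | Difference (points) |
|---|---|---|---|---|
| 0 | 4.5 | 1.8/4.5 = 40.0% | 2.4/4.5 = 53.3% | 13.3 |
| 50% | 3.6 | 0.9/3.6 = 25.0% | 1.5/3.6 = 41.7% | 16.7 |
| 100% | 2.7 | 0% | 0.6/2.7 = 22.2% | 22.2 |

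**Two assumed mixes, to see whether the ranking can change.**
- One of the three cytology-positive patients is ptDNA-negative (7, 1, 1, 2). The tests tie at 40.0% with no loss, but show 25.0% v 33.3% at 50% loss.
- Groups of 140, 15, 30 and 15, where cytology is truly the more sensitive test: 27/78 = 34.6% v 18/78 = 23.1% with no loss. They tie at 13.5/64.5 = 20.9% at 50% loss, and the order reverses at 75% loss, 6.75/57.75 = 11.7% v 11.25/57.75 = 19.5%.

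**Specificity.** The shift above concerns sensitivity. In the pilot mix the expected patients without an event are 4.9, 0.4, 0 and 1.2. The specificity difference (ptDNA minus cytology) goes from -0.4/6.5 = -6.2 points with no loss to -0.4/5.3 = -7.5 points at complete loss, a small move the other way. Cytology then reaches 100% specificity only because it has no positives left.

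**The case against.** The strongest reply is that the protocol expects cytology-positive patients to stay. Groups 3 and 4 are planned cohorts, 3 of 11 pilot patients were cytology-positive, and section 6a recruits patients already referred for curative-intent treatment, so intent may be meant as judged at recruitment. This stands as a reading of eligibility, but the text does not say so. It also leaves the second route open: a patient who is never resected has no DFS or OS, whatever date the exclusion carries.

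A reader might infer four stronger things that the documents do not support.

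- *That positive cytology triggers exclusion.* No section says this. It is an inference from the Background's account of how staging directs treatment.
- *That ptDNA must look better by construction.* This is certain only if every cytology-positive patient is lost. Otherwise it is a directional bias of unknown size. In the pilot mix ptDNA is ahead with no loss at all, so selection widens the gap but does not create it.
- *That ptDNA keeps all its positives.* It loses group 4, which held 3 of the 4 ptDNA-positive pilot patients, and its own sensitivity falls from 53.3% to 22.2%. Cytology's fall alone therefore does not measure the bias.
- *That two tests flagging the same patients could be ranked falsely.* With groups 2 and 3 empty the difference is zero. A false ranking needs group 3 patients, and the pilot had none.

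The 27% pilot share may also already reflect such selection, since section 5a describes that source cohort as identical to this one. The losses in the table are illustrations, not forecasts.

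**Conclusion.** The concern holds as a selection problem in the cytology part of secondary objective 2. As written, the plan allows cytology-positive patients to leave the analysis because of their cytology result, and the sensitivity comparison then moves towards ptDNA. In the pilot mix the gap grows from 13.3 points to 16.7 at an assumed 50% loss and 22.2 at complete loss. A change of ranking appears only under assumed mixes that include ptDNA-negative, cytology-positive patients.

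The figures rest on an 11-patient pilot, on the protocol's 40% and 70% DFS rates, and on equal loss in groups 3 and 4 that is unrelated to outcome. The direction does not depend on the pilot counts or DFS rates. The primary comparison and its sample size are unaffected. The point should be settled in the protocol, and it implies nothing about how cytology-positive patients ought to be treated.

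**What to change.** Reconcile the Synopsis (Design and Exclusion Criteria), section 4c, section 5a (study population), section 6c and section 8a as follows.

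1. State that treatment intent, for eligibility, is the intent planned at consent, before the cytology result, so that the result cannot exclude a patient already sampled.
2. Keep cytology-positive and unresected patients in groups 3 and 4 for ptDNA/cytology concordance and for OS counted from staging laparoscopy, the origin section 8a already uses for 2-year DFS. Take survival from routine records.
3. For resection-based DFS, make the added value of ptDNA among cytology-negative patients the main result of this objective. Label any head-to-head sensitivity or specificity against cytology in the resected cohort as subject to selection on cytology. The comparison need not be dropped.

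The cost is eligibility and endpoint wording, some extra survival follow-up of patients already consented, and a narrower DFS claim against cytology. Two limits remain. OS from laparoscopy will still reflect any treatment change that followed the cytology result, and this should be said when it is reported. Patients kept in groups 3 and 4 do not count towards the 175 + 25.
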